### Secondary Outcomes Measurement

Secondary outcomes are occurrence of CIN, performance of hemodialysis or hemofiltration and bleeding events at 4 weeks.

### Adverse effects

Analysis of safety related data is performed with respect to frequency of serious adverse events, frequency of serious adverse events stratified by causality and frequency of morbidity in both treatment groups.

At each assessment patients are assessed to report bleeding. Patients who experienced a bleeding event are further classified based on bleeding severity according to the Global Use of Strategies to Open Occluded Coronary Arteries (GUSTO) bleeding criteria [30]. Severe bleeding is defined as any intracranial hemorrhage or bleeding that causes hemodynamic compromise and requires intervention. Moderate bleeding is defined as bleeding requiring transfusion but does not result in hemodynamic compromise. Mild bleeding is defined as bleeding that does not meet criteria for either severe or moderate bleeding. Serious adverse events (SAE) have to be reported by the attending physician to the principal investigator within 24 hours after the SAE becomes known.

### Withdrawals

Patients are free to withdraw trial participation at their own request at any time and without giving reasons for their decision. Moreover, the primary investigator can withdraw study patients, if continuation of the trial would be detrimental to the patient's well being. Withdrawals will be documented in the Case report form (CRF) and in the patient's medical records and all ongoing SAE have to be followed up.

### Sample size

The sample size calculation is based on the primary outcome and the primary analysis for the intention-to-treat population. The sample size is calculated using the study's primary objective to detect a 50% difference of CIN occurrence between routine treatment with sarpogrelate and without sarpogrelate in a power of 80% to demonstrate difference. We assumed that the expected rate of CIN would be 20% in the control group [11]. We adjust the sample size for an estimated follow-up loss rate of 10%, a two-sided level of significance α = 5% and a power of 1-β = 80%, which result in 134 patients in each group is required to detect this difference with a two-sided Student's t- test. A total of 268 patients will be randomized and included in the analysis.

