## Background

Contrast-induced nephropathy (CIN) is a common form of hospital-acquired acute renal failure (ARF) after coronary angiography (CAG) and percutaneous coronary intervention (PCI) and is associated with prolonged hospitalization and adverse clinical outcomes [1,2]. Patients undergoing PCI have a higher mortality rate if the nephropathy develops [3]. Although its incidence is low in patients with normal renal function, it can be much higher in those with renal insufficiency at baseline [4,5]. Adequate prophylaxis is needed to reduce the higher morbidity and mortality associated with CIN in high-risk patients. A variety of therapeutic interventions, including saline hydration, diuretics, mannitol, calcium channel antagonists, theophylline, endothelin receptor antagonists, and dopamine, have been used in an attempt to prevent CIN [6-9]. Hydration with normal saline solution is the most widely accepted preventive intervention [9,10]. But the nephropathy occurred in 20~30% who received the recommend treatment [11,12], it means current treatments are not enough and the optimal strategy to prevent CIN has not been established.

Although the pathogenesis of this condition is not fully understood, it is most likely the result of renal ischemia and direct toxicity to tubular epithelial cells [13,14]. After contrast is injected, renal blood flow transiently increases and then decreases over a longer time, suggesting that renal ischemia is a major factor in the pathogenesis of CIN [13]. Contrast agents reduce the oxygen tension in both the cortex and the medulla [14]. Many studies suggest that contrast agents are directly toxic to kidney cells, causing proximal cell vacuolization, interstitial inflammation, cellular necrosis, and enzymuria [15].

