### Primary Outcome Measurement

The primary outcome of the study is the incidence of CIN, defined as either a greater than 25 percent increase of serum Cr or an absolute increase in serum Cr of 0.5 mg/dL within 48 hours after using contrast agent [28,29]. Clinical endpoint measurements are conducted in-hospital and at 4 weeks. Cr concentration is measured at admission, every day for the next two days after contrast exposure, and at 4 weeks.

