### Statistical analysis

The statistical analyses are performed on an intention-to-treat basis. The two-sided null-hypothesis for the primary outcome measure states that sarpogrelate has the potential effect on preventing CIN in CKD patients undergoing CAG or PCI. Descriptive statistics will be calculated according to the scale level of the variables. The Kaplan- Meier method is used to plot the time to the first episode of CIN, performance of hemodialysis or hemofiltration and bleeding events after CAG or PCI.

Continuous data will be analyzed using Student's t-test. The chi-square test is used for categorical variables. A value of p < 0.05 is considered statistically significant. Efficacy analyses was performed on the full analysis set, which consist of patients who received at least 1 dose of study medication. Patients who take the medication at least once are analyzed for safety. Graphical methods including scatter plots and boxplots will be used to visualize the findings of the trial.

The safety analysis includes calculation of frequencies and rates of complications and serious adverse events reported in the two groups. All analyses will be done using SPSS Version 16.0 or higher.

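### The sample size of 134 per group does not give 80% power for a fall in CIN from 20% to 10%; it gives about 58% to 63%

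*Protocol article*

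**What the plan says.** The protocol article defines a binary primary endpoint: "The primary outcome of the study is the incidence of CIN" (Primary Outcome Measurement).

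The Sample size section sets out all the inputs to the calculation:

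- Control rate: "We assumed that the expected rate of CIN would be 20% in the control group".
- Target: "to detect a 50% difference of CIN occurrence between routine treatment with sarpogrelate and without sarpogrelate". A drop of 50 percentage points from 20% is impossible, so this must be a relative reduction, 20% to 10%.
- Two-sided significance level 5%, power 80%, loss to follow-up 10%.
- Result: "which result in 134 patients in each group is required to detect this difference with a two-sided Student's t- test", hence 268 in total.

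The Randomization section gives 1:1 allocation. Two other places bear on the point. The Background reports that "the nephropathy occurred in 20~30% who received the recommend treatment", a range that starts at the assumed 20% and runs up to 30%. The Statistical analysis section states: "The chi-square test is used for categorical variables".

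**The concern.** All the inputs and the result are printed, so the calculation can be repeated from the article alone, and 134 is far too small for 20% versus 10% under the stated error rates. The test named in the sizing statement, Student's t-test, is one for continuous data and differs from the chi-square test that the analysis section assigns to categorical variables.

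What is at stake is the power claim for the trial's single primary hypothesis. If the section's own assumptions are true, the trial is much more likely to miss the effect than stated. A reader who trusts the 80% could then take a non-significant result as evidence that sarpogrelate does not work.

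**Working it through.** **Inputs.** p1 = 0.20 and p2 = 0.10, two-sided alpha 0.05 (z = 1.960), power 0.80 (z = 0.8416), loss 10% (all from Sample size), and 1:1 allocation (Randomization).

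**Formula (pooled variance under the null), per group.** With m = (p1 + p2)/2,

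n = [1.960·√(2m(1−m)) + 0.8416·√(p1(1−p1) + p2(1−p2))]² / (p1 − p2)²

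**Step 1: try to reproduce 134 from the stated inputs.** m = 0.15, so √(2 × 0.15 × 0.85) = 0.5050 and √(0.16 + 0.09) = 0.5.

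n = (0.9897 + 0.4208)² / 0.01 = 198.96, so 199 evaluable per group.

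After loss: 198.96/0.9 = 221.07, so 222 per group (444 in total). The shortfall is 222 − 134 = 88 per group. Other formulas do not close the gap:

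| Method, 20% vs 10% | Evaluable per group | After 10% loss |
|---|---|---|
| Pooled variance | 199 | 222 |
| Unpooled variance | 197 | 219 |
| Arcsine | 195 | 217 |
| Continuity-corrected | 219 | 244 |
| One-sided 5% (contradicts the section) | 157 | 175 |

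**Step 2: the power that 134 per group gives for 20% vs 10%.**

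Power = Φ{[0.10·√n − 0.9897] / 0.5}

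- n = 134 (no loss): (1.1576 − 0.9897)/0.5 = 0.336, power 63.1%.
- n = 120 (134 less 10% is 120.6): (1.0954 − 0.9897)/0.5 = 0.211, power 58.4%.

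Exact enumeration of the chi-square test gives 63.7% and 59.3%. The t-test applied to 0/1 data gives the same values to one decimal, so the choice of test does not explain the gap. A continuity-corrected chi-square test would have less power: 57.7% and 51.6%.

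**Step 3: what would justify 134.** Keep the 50% reduction, two-sided 5%, 80% power and 10% loss, and change only the control rate. For 30% vs 15%, m = 0.225:

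n = (1.1575 + 0.4889)² / 0.0225 = 120.47, and 120.47/0.9 = 133.86, so 134.

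Neighbouring rates do not fit: 29% gives 139 to 140 and 31% gives 128 to 129, depending on how loss is applied.

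**Step 4: the effect that the trial can detect from 20%.** With 120 evaluable per group, 80% power needs a fall from 20% to 7.6%, a reduction of (20 − 7.6)/20 = 62%.

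**Step 5: power for a halving across the Background's range** (same formula as in Step 2, with each pair of rates put in):

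| Control vs treated | 120 evaluable | 134 evaluable |
|---|---|---|
| 20% vs 10% | 58% | 63% |
| 25% vs 12.5% | 70% | 75% |
| 30% vs 15% | 80% | 84% |

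**The case against.** The mismatch itself has no good defence. The article prints both the inputs and the result, so brevity does not excuse it, and no standard formula connects them. The fair objections concern what is inferred from it.

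- **The origin of 134.** The match with 30% depends partly on rounding. If 120.47 is first rounded up to 121, then 121/0.9 gives 135, while 121 × 1.1 gives 134. Other routes also reach 134 if other inputs are altered, for example 25% vs 12.5% at one-sided 5%, or 20% vs 10% at one-sided 5% with 70% power. Each of these contradicts something the section states, as 30% does. This objection stands to the extent that 30% is a plausible source and not an established one.
- **Which power figure to quote.** CIN is defined within 48 hours of contrast, and the section says that all 268 patients will be analysed. The 10% loss may therefore fall mainly on the 4-week visit, which makes 63% the more natural figure. However, the Abstract and the Background describe the primary outcome over 4 weeks, so 58% cannot be ruled out. Both figures should be given, and both are well below 80%.
- **The t-test.** At these sizes it behaves almost exactly like the chi-square test on 0/1 data, and the analysis section already provides for chi-square. Naming it is a secondary slip in wording and does not explain the shortfall.

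**Conclusion.** The concern holds. On the section's own inputs, 134 per group is about 60% of the 222 required (134/222 = 0.60). Power for the stated target is 58% with the full 10% loss and 63% with none, so the claim of 80% is too high by 17 to 22 percentage points. This rests only on reading the 50% as a relative reduction, the sole reading possible from a 20% base, and on a standard two-sided comparison of two proportions. The 20% control rate and the 134 patients cannot both belong to the same calculation. Which of them was mis-stated cannot be settled from the document.

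**What to change.** Keep the planned size and correct the statement. The sponsor should retrieve the original calculation and then take one of two courses:

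1. If 20% was the intended control rate, state that 134 per group gives about 58% power (63% with no loss) to detect 20% versus 10% by a two-sided chi-square test at 5%.
2. If the records show that 30% versus 15% was the basis, correct the control rate to 30%, justify it, and show power for a halving across 20% to 30%: 58% to 80% with 10% loss, 63% to 84% without. This course should not be taken merely because 30% happens to fit.

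In either case, replace Student's t-test in the Sample size section with the chi-square test for two proportions, and write the target as a relative reduction with both rates given.

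The cost is a change of wording. No extra patients are needed to correct the statement, but the stated power for 20% versus 10% becomes less favourable. Restoring 80% power for that target would be a separate decision and would take 222 per group, 444 in total.

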### Randomization

Random assignments are generated using Excel spreadsheet software (Microsoft Corporation, Redmont, USA). Eligible patients are randomly assigned in a 1:1 ratio to receive routine treatment with sarpogrelate or routine treatment without sarpogrelate. Randomization is performed by a personnel not involved in the study and kept concealed.

### Statistical analysis

The statistical analyses are performed on an intention-to-treat basis. The two-sided null-hypothesis for the primary outcome measure states that sarpogrelate has the potential effect on preventing CIN in CKD patients undergoing CAG or PCI. Descriptive statistics will be calculated according to the scale level of the variables. The Kaplan- Meier method is used to plot the time to the first episode of CIN, performance of hemodialysis or hemofiltration and bleeding events after CAG or PCI.

Continuous data will be analyzed using Student's t-test. The chi-square test is used for categorical variables. A value of p < 0.05 is considered statistically significant. Efficacy analyses was performed on the full analysis set, which consist of patients who received at least 1 dose of study medication. Patients who take the medication at least once are analyzed for safety. Graphical methods including scatter plots and boxplots will be used to visualize the findings of the trial.

The safety analysis includes calculation of frequencies and rates of complications and serious adverse events reported in the two groups. All analyses will be done using SPSS Version 16.0 or higher.

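### The unadjusted test of 48-hour CIN is valid but leaves baseline eGFR, known for every patient before allocation, unused; adjusting for it is a small, low-cost gain in power

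*Protocol article*

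**What the plan says.** All references are to the protocol article.

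- **Outcome.** Under Primary Outcome Measurement the article writes: "The primary outcome of the study is the incidence of CIN, defined as either a greater than 25 percent increase of serum Cr". The alternative criterion is a rise of 0.5 mg/dL, and the window is 48 hours from contrast. Each patient has an event or does not. The Abstract and the stated hypothesis speak of CIN over 4 weeks instead; the outcome is binary on either wording.
- **Test (Statistical analysis).** "The chi-square test is used for categorical variables", with Student's t-test for continuous data. Kaplan-Meier is mentioned only for plotting. No model with a covariate appears.
- **Test (Sample size).** "134 patients in each group is required to detect this difference with a two-sided Student's t- test". This names a different test for the same comparison, also without adjustment.
- **Risk factor (Background).** CIN is said to be uncommon with normal renal function, but "it can be much higher in those with renal insufficiency at baseline".
- **Baseline data.** Eligibility depends on eGFR or serum creatinine (Participants). "Cr concentration is measured at admission" (Primary Outcome Measurement). Allocation follows a baseline measurement (opening of Methods/Design). The MDRD formula needs only creatinine, age and sex, so eGFR can be computed for everyone.
- **Allocation (Randomization).** "Random assignments are generated using Excel spreadsheet software", in a 1:1 ratio. No stratification factor is named.

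**The concern.** A baseline variable that predicts the outcome, is recorded for everyone and is fixed before allocation can be used to sharpen the treatment comparison at almost no cost. The article identifies such a variable, then states a primary comparison that does not use it, and it describes no stratification that would balance it by design.

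What is at stake is precision. With the stated test, outcome variation that eGFR could explain stays in the comparison as noise, so power is somewhat lower than the same data could give. This trial has little power to spare, as the working shows.

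**Working it through.** **1. The plan's own figure.** Inputs from Sample size: control rate 20%, a 50% reduction (so 10%), two-sided 5%, power 80%, 10% loss, 134 per arm.

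With p̄ = 0.15, the pooled two-proportion formula is

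n = [1.960·√(2·p̄(1−p̄)) + 0.8416·√(p₁(1−p₁) + p₂(1−p₂))]² / (p₁−p₂)²

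= [1.960·√0.255 + 0.8416·√(0.16 + 0.09)]² / 0.01 = (0.990 + 0.421)² / 0.01 ≈ 199 per arm.

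Allowing for loss, 199/0.9 gives 222. The 134 is not reproduced. Other variants, before and after loss:

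| Variant | Before | After |
|---|---|---|
| Continuity-corrected | 219 | 244 |
| Unpooled | 197 | 219 |
| Arcsine | 195 | 217 |
| t-test formula, SD √(0.15·0.85) = 0.357 | 201 | 224 |
| One-sided | 157 | 175 |

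**2. Power of the chi-square test at the planned size.** Power = Φ{[0.1·√n − 1.960·√0.255] / 0.5}.

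- n = 134: (1.158 − 0.990)/0.5 = 0.336, power 63%.
- n = 121 (134 × 0.9 = 120.6): (1.100 − 0.990)/0.5 = 0.22, power 59%.

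**3. What the covariate adds.** The article gives no strength for eGFR as a predictor among CKD patients, so the odds ratio per SD is an assumption, shown as a range. Trials were simulated with a standard-normal covariate, marginal rates held at 20% and 10%, and 134 per arm. To isolate the covariate, the same test (likelihood ratio in a logistic model) was used with and without it. There were 6,000 trials per setting, so each figure has a simulation standard error of about √(0.65·0.35/6000) = 0.6 points.

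| Assumed OR per SD | Power without eGFR | Power with eGFR | Difference (points) |
|---|---|---|---|
| 1.0 | 64.9% | 64.5% | −0.4 |
| 1.5 | 64.6% | 65.3% | +0.7 |
| 2.0 | 65.5% | 67.9% | +2.4 |
| 2.5 | 64.2% | 67.8% | +3.6 |
| 3.0 | 63.8% | 69.5% | +5.7 |

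At 120 per arm the gain is likewise about 0 to 6 points.

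Using the same test on both sides matters. When a Pearson chi-square is set against an adjusted likelihood-ratio test, power moves from 64.2% to 64.9% even at an odds ratio of 1.0, where the covariate carries no information. That part is a change of test, not a gain from eGFR.

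**4. The upper limit.** At an odds ratio of 4.5 per SD, a very strong predictor, the Pearson-versus-adjusted comparison goes from 63% to 74% at 134 per arm and from 59% to 70% at 121. Neither reaches 80%. Simulated type I error stayed near 5% for both tests.

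**5. Number of covariates.** Expected events are 134·0.20 + 134·0.10 = 40.2 with complete data, or about 36 with 120.6 per arm. That supports one pre-specified covariate comfortably, and not many.

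**The case against.** The strongest reply is that nothing here is an error. Under 1:1 randomisation an unadjusted chi-square test holds its level, and the choice is conventional. That stands. A reader might infer that chance imbalance in eGFR biases the result. It does not. With 134 per arm the standardised difference in mean eGFR has standard error √(2/134) = 0.12, so a gap above 0.2 SD arises in about 10% of trials; but the 5% level already allows for such gaps. Only efficiency is lost.

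Second, the Background contrasts normal with impaired renal function, whereas everyone enrolled has CKD. The named risk factor is therefore partly an entry criterion, and the article gives no gradient within CKD. This also stands, and it is why the gain is given as a range starting near zero. The outcome definition does tie risk to baseline creatinine to some degree: 25% of 2.0 mg/dL is 0.5 mg/dL, so above 2.0 a rise of less than 25% can qualify. That shows a dependence is possible, not how strong it is.

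Third, the chi-square sentence is a general rule in a condensed article, and strata or covariates may be set out elsewhere. This stands in part. A reader might infer that randomisation was unstratified; the article supports only that no stratification is described. It does state its tests, however, and neither of the two it attaches to this comparison uses the baseline value.

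Fourth, low power belongs to the sample-size calculation. That is right, and adjustment should not be presented as its remedy.

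**Conclusion.** The point holds as a low-severity efficiency gain. The primary comparison is unadjusted under either named test, although a baseline variable that the article itself links to CIN is available for every patient before allocation. The loss is about 0 to 6 points of power, resting on an assumed odds ratio of 1.5 to 3.0 per SD of eGFR within CKD, an approximately linear effect on the logit scale, and the article's own rates of 20% and 10%. If the gradient within CKD is weak, the gain is negligible.

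Two stronger conclusions are not supported. The stated test is not invalid. Nor would adjustment deliver what the article claims, "in a power of 80% to demonstrate difference": the shortfall from 80% to about 63% (59% after loss) comes from the sample size and remains a separate, larger problem. The conflict between the t-test in Sample size and the chi-square test in Statistical analysis is a plain inconsistency that needs resolving whether or not the analysis is adjusted.

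**What to change.** State one primary analysis, in the same words in Sample size and Statistical analysis:

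- Logistic regression of 48-hour CIN on treatment, with baseline eGFR (MDRD, pre-contrast) as one pre-specified continuous covariate.
- Report the standardised (marginal) risk difference with 95% CI: the mean predicted risk over all analysed patients with treatment set to sarpogrelate, minus the same mean with treatment set to control. This keeps the estimate on the absolute-risk scale and avoids reading a conditional odds ratio as a marginal effect.
- Keep the unadjusted chi-square test as a supporting analysis.
- If allocation was in fact stratified, say so and include the stratification factors in the model.

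Because the trial is not blinded, fix and date this before any outcome comparison by arm, so that the choice of covariate cannot be questioned later.

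The cost is wording only, with no new data and no change to patient care. The downside is an estimate slightly harder to explain than a two-by-two table. The sample size must be dealt with separately.

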## Methods/Design

The study is designed as a non-blinded, prospective, randomized controlled clinical trial to evaluate efficacy and safety of sarpogrelate in CKD patients undergoing CAG and PCI. After a baseline measurement, participants were randomly allocated into the treatment group (routine treatment with sarpogrelate) or the control group (routine treatment without sarpogrelate). In this study, routine treatment is defined as saline hydration and benefit of sarpogrelate is assessed as an adjunct to saline hydration for the prevention of CIN following diagnostic CAG or PCI

Study approval was given by the Ethics Committee/Institutional Review Board of Seoul National University Boramae Medical Center.

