### Intervention

After a baseline measurement, all patients receive 0.9% saline or 0.45% saline intravenously at 150 ml/hour at least for 6 hours before and 6~8 hours after receiving contrast agent. Patients in the treatment group receive sarpogrelate 300 mg per day for 24 hours before exposure to contrast agent. Sarpogrelate will be given for 4 weeks.

Recruitment of participants started in April 2010. The process of the trial conduct is illustrated in Figure 2. No additional risks for study patients are expected, since all treatment is carried out within established standard methods of CAG or intervention.

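### The efficacy set requires a dose of study medication that the open-label control arm never receives, which contradicts the stated intention-to-treat analysis of all 268 randomised patients

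*Protocol article*

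**What the plan says.** All of this is in the protocol article.

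- **Statistical analysis**, basis: "The statistical analyses are performed on an intention-to-treat basis".
- **Statistical analysis**, efficacy set: "Efficacy analyses was performed on the full analysis set, which consist of patients who received at least 1 dose of study medication".
- **Statistical analysis**, safety set: "Patients who take the medication at least once are analyzed for safety". The same section reports complications and serious adverse events for both groups.
- **Sample size**: the calculation is made for the intention-to-treat population, with 134 patients per group. "A total of 268 patients will be randomized and included in the analysis".
- **Methods/Design**: the trial is non-blinded, and the comparator is "the control group (routine treatment without sarpogrelate". Further, "routine treatment is defined as saline hydration and benefit of sarpogrelate is assessed as an adjunct to saline hydration".
- **Intervention**: "all patients receive 0.9% saline or 0.45% saline intravenously". Only the treatment group is given sarpogrelate, starting before contrast. No placebo is described anywhere.

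**The concern.** A one-dose condition is often tolerable in a blinded placebo trial, because both arms have something to take and the condition falls on them alike. Here only one arm has a drug to take, so the condition cannot work the same way in both.

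Who enters the primary comparison is at stake. If randomised patients are dropped from one arm according to something that happened after allocation, the two groups compared are no longer the randomised ones. In an open-label trial, failure to take a first dose may depend on knowing the allocation or on the patient's clinical course. The article also leaves two incompatible rules for the same analysis, and the choice between them should not remain open once outcomes by arm can be seen.

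**Working it through.** **Step 1. What the efficacy rule does to each arm.** Inputs: 134 per group and 268 in total (Sample size); sarpogrelate in the treatment group only (Intervention); no placebo.

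| Reading of the one-dose rule | Sarpogrelate arm | Control arm | Agrees with intention-to-treat and 268 analysed? |
|---|---|---|---|
| Literal: sarpogrelate must have been taken | dosed patients only | 0 of 134 | No; no comparison is possible |
| Applied to the sarpogrelate arm only | dosed patients only | all 134 | No; exclusion from one arm |
| Saline counted as study medication | patients given saline or drug | patients given saline | No; randomised patients given neither are dropped |

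The third reading would remove the asymmetry, but the text does not support it. Methods/Design calls saline routine treatment and sarpogrelate the adjunct being assessed.

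**Step 2. Possible bias under the one-arm reading.** The only input from the article is the 20% control rate (Sample size). Assumed: no drug effect, so 20% risk in each full arm; a share d of the sarpogrelate arm never dosed; risk r of contrast-induced nephropathy (CIN) in those patients. Then

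rate among the dosed = (0.20 − d × r) / (1 − d).

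| r in the undosed | d = 5% | d = 10% |
|---|---|---|
| 40% | 0.180/0.95 = 18.9% | 0.160/0.90 = 17.8% |
| 30% | 0.185/0.95 = 19.5% | 0.170/0.90 = 18.9% |
| 20% | 0.190/0.95 = 20.0% | 0.180/0.90 = 20.0% |
| 10% | 0.195/0.95 = 20.5% | 0.190/0.90 = 21.1% |
| 0% | 0.200/0.95 = 21.1% | 0.200/0.90 = 22.2% |

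Against 20% in the controls, the spurious difference runs from 2.2 points in favour of sarpogrelate, through zero, to 2.2 points against it. The planned effect, reading the 50% difference as 20% versus 10%, is 10 points.

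**Step 3. Effect on the test.** For the 40%-risk cases, a normal approximation to the two-sided 5% test of two proportions, with 134 controls and 134 × (1 − d) dosed patients, gives a type I error of about 5.5% (d = 5%) and 7.3% (d = 10%).

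**Step 4. Loss of numbers.** The one-arm reading leaves about 131, 127 or 121 sarpogrelate patients if 2%, 5% or 10% are undosed. Power for 20% versus 10% moves from 63.1% (134 versus 134) to 62.6%, 61.8% or 60.3%. The starting value is below the stated 80% because 134 does not follow from the stated inputs: the usual formula gives [1.96 × √(2 × 0.15 × 0.85) + 0.842 × √(0.16 + 0.09)]² / 0.10² = 199 per group, and 199/0.90 = 222 after 10% loss. That is a separate matter, and nothing in this point depends on it.

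**Step 5. The safety rule.** Read literally, no control patient enters the safety set, yet safety is to be reported for both groups (Adverse effects; Statistical analysis). Read as applying to the sarpogrelate arm only, the controls stay and the comparison survives.

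**The case against.** The strongest reply is that nobody intends an analysis without controls. The hypothesis at the end of the Background compares sarpogrelate with the control group, safety is promised for both groups, and all 268 patients are to be analysed. This stands: the literal reading shows a faulty definition, not a likely result. A reader might infer that the trial will have no comparator; the rest of the article rules that out. The more workable one-arm reading is still not intention-to-treat.

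A reader might also infer that the rule favours sarpogrelate. The article does not support a direction. Undosed patients could be at higher risk, but a patient who withdraws before both drug and contrast could have little or no CIN risk, and exclusion would then count against the drug. At equal risk there is no bias.

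A third tempting inference is that the safety rule breaches intention-to-treat, or that the bleeding comparison is lost on any reading. A one-dose safety set is usual for a treated arm and breaches nothing in itself, and the comparator is lost only on the literal reading. What stands is that the rule does not say how controls qualify.

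Finally, an analysis plan not shown here may define the sets properly. But the article does not defer the definition: it states one, and that one conflicts with its own stated basis.

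**Conclusion.** The concern holds as a contradiction in the definition of the efficacy set, and that conclusion needs no numerical assumption. Both the literal and the one-arm reading are incompatible with the intention-to-treat basis and with the inclusion of all 268 randomised patients. The safety set has the lesser fault of leaving controls without a stated place.

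The consequence for the estimate cannot be sized from the article. With 5-10% undosed and a CIN risk of 0-40% in them, all assumed, the spurious difference lies within 2.2 points either way, modest beside the planned 10 points. The case for correction rests on having one unambiguous primary population fixed before open-label results are seen, not on a demonstrated bias.

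**What to change.** - **Efficacy.** Define the primary efficacy set as all randomised patients, analysed in the arm to which they were assigned, and delete the one-dose condition.
- **Safety.** State that the safety set includes the control patients, with patients grouped by whether sarpogrelate was taken.
- **Optional.** If a modified efficacy set is wanted, define it by a condition that applies identically to both arms, and use it as a sensitivity analysis only.

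The cost is a change of wording. Keeping undosed patients may dilute the effect slightly: if 5-10% are undosed with 20% risk and the dosed have 10%, the 10-point difference becomes 10 × 0.95 = 9.5 to 10 × 0.90 = 9.0 points.
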